### Interventions

#### Parent-infant psychotherapy

Parent-Infant Psychotherapy (PIP) is a manualised focus-based short-term psychodynamic psychotherapeutic intervention that we have developed ([name], [name], [name]: SKKIPPI Study manual for Parent-Infant-Toddler Psychotherapy (PIP), Unpublished), which includes the children and their primary caregivers ([11, 25]; [name], [name], [name]: SKKIPPI Study manual for Parent-Infant-Toddler Psychotherapy (PIP), Unpublished). Generally, the therapist works with the parents (or other important caregivers) and the infant in joint sessions. In special situations (for example, if the mother has depressive symptoms) there may be a few sessions with one parent alone, in order to address important themes that cannot be addressed in joint sessions. The intervention focuses mainly on the meaning the parents ascribe to their child’s symptoms. The therapist observes the parent-child interaction and tries to link his/her observation to the parental beliefs and interpretations. The therapeutic focus includes the family history, parental thoughts, symptoms, and the therapeutic relationship that develops during the sessions. The aim of the therapist’s intervention is to help the parents to understand and to ‘contain’ the child’s affective states. The intervention builds on parental self-reflection and supports the parental ability to mentalise. PIP also aims to strengthen specific parental ego functions.

The focused psychodynamic psychotherapy is conducted in 12 sessions, twice a week over a period of 6 weeks. The course of PIP is divided into three phases: the initial diagnostic phase, the second phase of the focused intervention, and the third and final phase of integration. The therapists are trained to consider the parents’ couple relationship, the personalities of the parents, and possible conflicts in the mother-father-infant triads. The therapists try to create a holding environment for parents and infant within the therapeutic sessions. The holding therapeutic function helps participants to clarify problems, regulate affects, engage in self-reflection, and change their perspectives, and thus provides support for interpersonal resources in the parent-child triad. Psycho-education and the use of video feedback are additional therapeutic options for the intervention, which is oriented towards the mother’s psychodynamic, structural level. Video feedback can be used if there are maternal developmental deficits and a space of self-perception with the child cannot be created in inner presentations and phantasies.

At the end of the intervention, the therapist encourages the parents to reflect upon their experience of the therapeutic process and to develop strategies for using the therapeutic experience in their everyday life. The treatment technique is manualised and follows guidelines according to the setting. Every therapist undergoes specialised training according to the manual before the first session to ensure adherence to the treatment techniques described within it. All therapists are either psychodynamic psychotherapists (psychologists and medical doctors) or psychologists and medical doctors in advanced psychodynamic psychotherapy training. The therapies are supervised by experienced PIP therapists at regular intervals in order to secure treatment fidelity (Fig. 2).

**Fig. 2 Fig2:**
[figure not shown]
Indication and Procedure for Parent-Infant Psychotherapy

#### Control group: care as usual

Patients in the control group receive standard medical, pedagogical, and/or psychotherapeutic care for 6 weeks, as usually provided by the German health care system. Ethical considerations mean the control group could not be designed as a no treatment control. In the inpatient setting, more care might be provided than in outpatient settings. This could include counselling, physical or psychotherapy, and other psychiatric-therapeutic interventions. Outpatient settings may be either therapeutic or pedagogical care. Because of possible heterogeneities in the number and intensity of CAU treatments compared to PIP, all individual interventions will be documented in detail.

### Outcomes

#### Primary outcome

The primary outcome will be maternal sensitivity measured after 6 weeks of intervention. Videotaped dyadic sessions of free-play interaction will be coded using the subscale ‘sensitivity’ of the emotional availability scales (EAS) [30]. EAS assesses the quality of the mother-child interactions using a seven-point Likert scale for maternal sensitivity. Independent and reliable coders blind to treatment allocation rate all the 15- to 20-min video scenes.

### Secondary outcomes

#### Child attachment

The most important secondary outcome will be the child’s attachment style, measured using the Strange Situation Procedure (SSP) for children up to 20 months [31]. The SSP is a standardised procedure recording eight episodes to rate the child’s attachment quality to his or her caregiver. Attachment security is rated by independent coders blind to treatment allocation. The classification can be secure (B), avoidant (A), or ambivalent (C). Disorganised (D) attachment qualities will also be scored.

The attachment style of children older than 20 months is assessed using Attachment Q-Sort (AQS) [32]. The AQS evaluates the degree of attachment security for infants aged 12 to 48 months, and is a one- to two-hour procedure in which the child and its mother are observed in their home environment. The infant’s behaviour is evaluated by the observer for 90 standardised Q-Sort items, which are compared to a typical profile of securely attached children. The AQS varies on a scale between − 1 and 1, and does not reflect the variety of attachment categories, as the SSP does.

#### Maternal mental health problems

Maternal mental health problems are assessed using the Brief Symptom Checklist (BSCL) [35], a validated questionnaire to measure adult psychopathological symptoms, at 6 weeks follow-up. A further questionnaire assessing mental health status, the Anxiety Screening Questionnaire (ASQ-15) [36], covers all anxiety disorders diagnosed by DSM IV and ICD-10. Mothers complete the questionnaire at 6 weeks follow-up. The Scale for Impulsive Behaviour and Emotional Dysregulation of Borderline Personality Disorder (IES-27) [37] is a screening instrument to measure typical patterns of BPD. The IES-27 questionnaire is assessed at 6 weeks follow-up. Symptoms of maternal depression are measured using the Edinburgh Postnatal Depression Scale (EPDS) [38] at all measurement points. To explore psychiatric disorders, the Mini International Neuropsychiatric Interview (M.I.N.I.) [39], a structured diagnostic interview, which assesses 20 psychiatric disorders by DSM IV and ICD-10 diagnosis, is used. The M.I.N.I. assesses possible maternal clinical diagnoses and will be administered by trained interviewers at 12 months follow-up.

#### Maternal attachment and reflective functioning

Maternal attachment style and reflective functioning, i.e. the capacity to mentalise, are considered essential moderators in the present design and are assessed using the Adult Attachment Interview (AAI) [40]. The AAI is a semi-structured interview with precise psychometric properties to evaluate the maternal ‘state of mind’ with respect to attachment. The AAI is conducted by trained interviewers, transcribed, and subsequently scored by reliable and independent coders blind to treatment allocation.

#### Developmental status of the child

The standardised German developmental test ET 6–6 R [41] assesses the level of social-emotional, cognitive, motor and language development of children aged between 6 months and 6 years. The developmental status of the child is evaluated at all three measuring points. In addition, and at the Leipzig study centre subgroup only (due to availability reasons), the Bayley Scales of Infant and Toddler Development (Bayley-III) [42] is assessed. Bayley-III depicts the developmental level of infants aged between 0 and 42 months in a differentiated manner based on various subtests.

#### Psychological factors

The Parental Stress Index (PSI) [43] is used to measure maternal parental stress, and the Parental Reflective Functioning Questionnaire (PRFQ) [44] to measure the mother’s self-reported ability to mentalise in the context of her relationship to her child. Both questionnaires are assessed at 6 weeks, and 12 months follow-up.

Additionally, the five further subscales of the EAS based on the 15-min videotaped mother-child interactions (maternal dimensions: structuring, non-intrusiveness and non-hostility; and child dimensions: responsiveness to parent, involvement with parent) are analysed as secondary outcomes. Free-play sessions are recorded at all measurement time-points and rated by reliable and independent coders blind to treatment allocation.

#### Treatment adherence

Treatment Adherence is assessed using an in-house questionnaire with 30 items to evaluate the methods and interventions applied by the PIP therapist after each session.

#### Health care and social service utilisation

Another questionnaire we have developed also assesses the economic consequences of using health and social care, and requests for early intervention services. Mothers complete the questionnaire at 12 months follow-up. The utilisation documented will be analysed to assess the associated costs (Fig. 3).

**Fig. 3 Fig3:**
[figure not shown]
Full Standard Protocol Items: Recommendations for Interventional Trials (SPIRIT); PIP – Parent-Infant Psychotherapy, CAU – care as usual, EAS – Emotional Availability Scales, SSP – Strange Situation Procedure, AQS – Attachment Q-Sort, DC:0–5 – Diagnostic Classification of Mental Health and Developmental Disorders of Infancy and Early Childhood (Interview), CBCL – Child Behaviour Checklist, SFS – Crying Feeding Sleeping Questionnaire, BSCL – Brief Symptom Checklist, ASQ-15 – Anxiety Screening Questionnaire, IES-27 – Scale for Impulsive Behaviour and Emotional Dysregulation of Borderline Personality Disorder, EPDS – Edinburgh Postnatal Depression Scale, M.I.N.I. – Mini International Neuropsychiatric Interview, AAI – Adult Attachment Interview, ET 6–6 R – German developmental test, Bayley-III – Bayley Scales of Infant Development, PSI – Parenting Stress Index, PRFQ – Parental Reflective Functioning Questionnaire

### Data collection and monitoring

Researchers responsible for data collection are blind for randomisation and treatment group allocation. All data are stored under pseudonyms until the whole study is terminated. Data on the intervention will be unblinded after the last participant has completed the study. Only pseudonymous data sets will be analysed. There are formal rules for stopping the trial should a severe adverse event (SAE) occur. In the case of SAE the advisory board will be consulted. The consortium leader (LK) will report any SAE to the local ethics committees and all relevant parties. Standard operating procedures (SOPs) will be activated and will lead to exclusion of the participant and potentially to the termination of the trial. The participating scientists and study therapists are trained and qualified in all methods. All study therapists will receive training in PIP according to the SKKIPPI study manual. The SKKIPPI study manual is also the basis for the regular therapy adherence measurements.

The study centres are monitored based on the data collection status (mutual monitoring of the study centres by the study team) to ensure completeness and compliance with ethical considerations.

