### Trial design

The two-armed, open, randomised, controlled multicentre study with parallel groups and blinded endpoint assessment (PROBE design; prospective randomised, blinded endpoint) with a six-week intervention is currently underway in Leipzig, Berlin, Potsdam and Hamburg. All study centres and participating clinics there provide focused and supervised certified PIP in accordance with a previously elaborated SKKIPPI Study Manual ([name], [name], [name]: SKKIPPI Study manual for Parent-Infant-Toddler Psychotherapy (PIP), Unpublished). Depending on the severity of the child’s pathological symptoms, and in agreement with parental preferences, a decision is made on treatment setting (in−/outpatient) before randomisation. Participants are then randomly assigned to either PIP or CAU, and data are collected at three measurement points: at baseline before intervention, immediately after treatment, and at 12 months follow-up. The biostatistician of the Institute for Social Medicine, Epidemiology, and Health Economics at the Charité – Universitätsmedizin Berlin generates the allocation sequence based on a computer generated random list, applying a 1:1 block randomisation with variable block length and stratified by setting (inpatient/outpatient) and study centre. Mother-child dyads are randomly assigned to either PIP or CAU.

Before being enrolled in the trial, participants are screened by a professional physician or psychotherapist for eligibility and clinical diagnoses. Only children receiving an ICD-10 diagnosis of regulatory disorder can take part in the study. Eligible mothers of these children are informed verbally about the study, and written informed consent must be given before randomisation. Afterwards, baseline assessments are carried out, and the 6 weeks of interventions start. At the end of treatment, participants are assessed again, as well as 12 months after baseline. Mothers will receive €100 as monetary compensation (25€ after Baseline, 25€ after 6 weeks follow-up and 50€ after the last assessment) until the 12-months follow-up. Throughout the study, the study nurse is in contact with the participants via phone calls or e-mails to schedule appointments. Treatment allocation is masked to the assigning personnel and there are no special criteria for discontinuing or modifying the allocated intervention (Fig. 1).

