### Data analyses

#### General considerations and socio-demographic data

Socio-demographic and clinical information are described at baseline using frequencies and percentages (e.g. categorical variables) or means and standard deviations (e.g. continuous variables), and treatment conditions compared to assess potential baseline differences. The statistical analyses are based on all mother-child dyads included in the study after randomisation (Fig. 1), according to ITT (Intention to Treat) principles. The data to be used in all analyses (unless otherwise stated) is defined as the Full Analysis Set (FAS) and includes all mother-child dyads after randomisation, irrespective of the treatment received. Data from mother-child dyads who drop out of the study are included in the FAS up to the date they withdraw. The Per Protocol (PP) population is a subset of the FAS and includes mother-child dyads who conform to the study plan (i.e. sufficient treatment adherence, no major protocol violations). The safety population is defined as mother-child dyads who have participated in at least one intervention session, and is analysed according to the treatment they received.

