#### Primary endpoint

The primary analysis of the primary endpoint (maternal sensitivity measured using the EAS subscale after 6 weeks) will be analysed using ANCOVA based on the FAS population using PIP versus CAU as the factor treatment group, EAS sensitivity at baseline as covariate, and the stratification variable treatment setting. Results will be displayed as adjusted means of the treatment group together with 95% confidence intervals and the respective *p* value (two-sided). The significance level is set at α =0.05. All further analysis is considered exploratory.

A secondary analysis of the primary endpoint will also be carried out using the ANCOVA model based on the PP population. Additional moderator analyses of the efficacy of PIP for a change in maternal sensitivity (EAS) will be conducted with treatment setting as the moderator, i.e. by additionally adding a ‘treatment group’ * ‘treatment setting’ interaction term to the model. Further moderator analyses regarding the efficacy of PIP will comprise maternal attachment type (AAI attachment) or maternal reflective functioning (AAI RF) as moderators.

In addition, models incorporating multiple imputation methods based on the PP population and a hierarchical regression model (including the therapist as a grouping factor and therapist’s adherence as covariate) will be used for sensitivity analyses of the primary outcome. To investigate the longitudinal change of the primary endpoint, linear mixed models (LMMs) incorporating both measurement points for each outcome (FAS population) will be computed. To explore further effects of additional predictors (such as the therapists carrying out the interventions), the models will be compared based on model fit values (AIC, the Akaike Information Criterion), with these predictors included in the model term.

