#### Missing data

After written informed consent and randomisation, participants can be excluded from the analyses only if there has not been any intervention, no data have been collected after randomisation, or at the participants’ express request after withdrawing from the study during the data collection phase. Primary statistical analyses of the primary and secondary endpoints are based on the FAS population without the imputation of missing data. For a sensitivity analysis, missing values for the primary endpoint will be imputed using Multiple Imputation methods for linear regression based on Markov chain Monte Carlo (MCMC) simulations. Imputation variables will be selected blinded for the intervention groups, and at least 5000 iterations and 100 imputations will be calculated.

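### The plan says an SAE leads to exclusion of the participant, and does not say that outstanding assessments are still collected

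*Protocol article*

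**What the plan says.** Protocol article, Data collection and monitoring: "In the case of SAE the advisory board will be consulted". The SAE is reported to the ethics committees, and operating procedures are activated that "will lead to exclusion of the participant and potentially to the termination of the trial". The word *potentially* qualifies termination of the trial only. Exclusion of the participant is stated without a condition.

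Other sections bear on what happens next:

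- **Trial design** schedules later assessments for every dyad: "At the end of treatment, participants are assessed again, as well as 12 months after baseline". It also says that no special criteria exist for stopping or changing the allocated intervention.
- **General considerations and socio-demographic data** defines the FAS as a set that "includes all mother-child dyads after randomisation, irrespective of the treatment received". Dyads who drop out contribute data up to the date they withdraw.
- **Missing data** gives a closed list: "participants can be excluded from the analyses only if there has not been any intervention", if no data were collected after randomisation, or if the participant asks for it. An SAE is not on the list. Primary analyses of the primary and secondary endpoints "are based on the FAS population without the imputation of missing data". As a sensitivity analysis, "missing values for the primary endpoint will be imputed using Multiple Imputation methods"; secondary endpoints are not mentioned there.
- **Primary endpoint** tests 6-week maternal sensitivity and then states: "All further analysis is considered exploratory".

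**The concern.** An SAE happens after randomisation and may be related both to the assigned care and to how the dyad is doing. If the trial's own rule ends observation at that point, the later outcome is missing for a reason that may be informative, even when the mother would have been willing to continue. Analysis by intention to treat needs outcomes as well as membership of the analysis set. A dyad that stays in the FAS but has no 12-month assessment adds nothing to a 12-month comparison run without imputation.

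The outcomes most exposed are those collected only late. Child attachment is named the most important secondary outcome, and a higher rate of secure attachment at 12 months is an explicit hypothesis under Aims and hypotheses. The utilisation questionnaire, which feeds the cost analysis, is also completed at 12 months. Later harms in the same dyad could go unrecorded too.

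**Working it through.** **Step 1: what exclusion can mean.** The article does not define the word. Three readings are possible.

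| Reading | Checked against | Result |
|---|---|---|
| Removed from the analyses | FAS definition; closed list under Missing data | Ruled out: an SAE is not a listed ground |
| Study treatment stopped, follow-up continues | Trial design: no special criteria for stopping the intervention | No data lost, but fits poorly with Trial design |
| Dyad leaves the study | Trial design: 6-week and 12-month assessments | Assessments outstanding at the SAE are not collected |

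The third is the plain sense of the phrase, and no sentence in the article overrides it. The steps below assume it.

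**Step 2: what the analysis plan recovers.** Linear mixed models are planned for the primary endpoint in the FAS, and for maternal stress, parental reflective functioning and infant symptoms across all measurement points. These use a dyad's earlier records. The analysis of 12-month attachment is a logistic regression without imputation, and utilisation is recorded at 12 months. Neither can be recovered from earlier records of the same measure.

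**Step 3: number of dyads.** The documents give N = 160, 80 per arm and 20% dropout; they give no SAE rate. Assume a fraction p = 1%, 2% or 5% of dyads has an SAE over 12 months, spread evenly in time, so that 6/52 = 0.115 fall before week 6.

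| p | Lost, 160 × p | Before week 6, × 0.115 | After week 6 |
|---|---|---|---|
| 1% | 1.6 | 0.18 | 1.42 |
| 2% | 3.2 | 0.37 | 2.83 |
| 5% | 8.0 | 0.92 | 7.08 |

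The dropout allowance is 160 × 0.20 = 32 dyads, so the loss equals 5%, 10% or 25% of it.

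**Step 4: primary endpoint, power.** The plan's inflation reproduces: 64/(1 − 0.20) = 80 per arm. At d = 0.64, two-sided α = 0.05, a t-test without covariate has 94.9% power with 64 per arm. The plan states 90%; about 53 per arm would give that. The difference is on the safe side and does not bear on this point. Taking the SAE loss on top of the 20% dropout:

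- p = 1%: 64 − 0.18/2 = 63.91 per arm, power 94.85%.
- p = 5%: 64 − 0.92/2 = 63.54 per arm, power 94.73%.
- Harsh case, 5% all lost before week 6: 80 × (1 − 0.20 − 0.05) = 60 per arm, power 93.5%.

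**Step 5: primary endpoint, bias.** Shift = difference in SAE rate between arms × fraction before week 6 × outcome gap. With an assumed 3-point difference and a gap of 1 SD: 0.03 × 0.115 × 1 = 0.0035 SD. With equal rates and equal gaps, or no gap, it is 0. The direction depends on which arm has more SAEs.

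**Step 6: 12-month attachment.** With the same 3-point difference, and lost children differing from the rest by 20–40 points in the share securely attached: 0.03 × 0.20 = 0.6 points to 0.03 × 0.40 = 1.2 points. Worst case, with 50% secure among those observed and a fraction m lost in each arm: (m + m) × 0.5 = ±1, ±2 or ±5 points for m = 1%, 2% or 5%. For scale, the 95% confidence interval half-width with 64 per arm is 1.96 × √(2 × 0.25/64) = 17.3 points.

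**The case against.** The strongest reply is that the consequence hangs on an undefined word. The operating procedures are not shown, and a journal article may leave SAE handling to them. If they define exclusion as stopping study treatment, no data are lost. That stands, and it is why the loss of follow-up is stated conditionally. It does not remove the point: the article itself says what the procedures do, and says it without a condition.

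Second, ending follow-up may be unavoidable. Acute psychosis, suicidal tendencies and acute substance abuse are exclusion criteria at entry. After an SAE of that kind the mother may be unable to take part, and no wording would secure the assessment. This stands, and the fix allows for it.

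Third, a reader might infer more than the documents support:

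- *That dyads with an SAE are dropped from the analysis, breaking intention to treat.* The closed list and the FAS definition rule this out. Early end of follow-up is a missing-data problem inside that definition.
- *That both the 6-week and the 12-month assessments are lost.* Only those still outstanding are. With even timing, about 88% of SAEs fall after week 6, and those dyads have passed the primary assessment.
- *That the harm itself goes unrecorded.* The triggering SAE is reported to the ethics committees and all relevant parties.
- *That the primary result is at risk.* The figures above do not support this.

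**Conclusion.** The point holds as a minor one. The protocol article states an unconditional rule of exclusion after an SAE and nowhere says that assessments continue. Read plainly, the rule stops collection of whatever is still outstanding, chiefly 12-month attachment and utilisation.

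The likely effect is small: 1.6–8 of 160 dyads, of which at most about one is lost before week 6; power for the primary endpoint near 95%; a primary shift of 0 to 0.0035 SD in either direction; and a 0.6–1.2 point shift in secure attachment against a half-width of about 17 points. The attachment and utilisation outcomes are exploratory under the plan.

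Every one of these sizes rests on assumptions that the documents do not supply: an SAE rate of 1–5%, even timing, a 3-point difference between arms and the stated outcome gaps. They also assume that exclusion means leaving the study. If the operating procedures mean only stopping treatment, the loss is nil and the sentence simply needs to say so.

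**What to change.** Under Data collection and monitoring, replace the statement that the procedures lead to exclusion of the participant with:

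> An SAE may lead to stopping study treatment on clinical judgement after consultation with the advisory board; where consent holds and the mother is able to take part, the dyad continues the scheduled 6-week and 12-month assessments and safety recording, and remains in the FAS.

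The possible termination of the trial can stay as it is. Under Trial design, cross-reference this as a possible reason for discontinuing the allocated intervention, so that the two sections agree. Align the operating procedures.

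The cost is wording only. The assessments are already scheduled for every dyad, so no visits are added. Participant protection is unchanged, because treatment can still be stopped and consent withdrawn.
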